### Recruitment & retention

Our recruitment plan is guided by the successful processes we have implemented in prior community-based studies [36]. ASHAs are women residents of the community who are selected to be trained and deployed to work alongside the local PHC to improve the health of all community residents by ensuring they have access to medical treatment; their trifold role includes that of a health activist, link-worker, and a community health worker, all of which make them an ideal fit for their study role in identifying and referring potentially eligible couples within their community. The ASHA will identify couples they know are experiencing IPV in which the husband is also using alcohol. Following consultation with the research team, the ASHA will bring the couple to the PHC, the Namma Clinic (an urban healthcare and wellness centers affiliated with the PHC), or community spaces owned by local private and religious organizations for screening.

The intervention will be presented to participants as one that is aimed at enhancing communication and improving relationship quality between spouses (and, critically, not an IPV intervention). The wife will be screened using the SBT [73] to rule out cognitive deficits impeding optimal study participation, AUDIT-C to rule out AUD, [68] and IVAWS [67] to identify physical and/or sexual violence in the past 12 months and to rule out violence severe enough to have resulted in the woman being admitted at a hospital or lodging police complaints. The husband will be screened using the SBT to rule out cognitive deficits impeding optimal study participation, [70] AUDIT-C to identify AUD (score>4), [67] SADQ to rule out severe alcohol dependence (score≥31), [69] and CIWA-AR to screen out participants who are at high risk of developing withdrawal symptoms (score≥8) [70]. Based on our prior experiences, we conservatively estimate needing to screen 2,350 couples to enroll 400. All participants who are ineligible for the study but screen positive for AUD and/or IPV will receive a brief educational session [74] and a referral to the National Institute of Mental Health and Neurosciences (NIMHANS) in Bangalore, a premier tertiary care institute which offers counseling and psychiatry services as well as a dedicated de-addiction treatment for severe alcohol dependence and alcohol withdrawal.

Research staff will screen and obtain informed consent with the spouses separately. Due to varying literacy levels, the informed consent form will be read aloud to the participant. The participant will be asked to narrate back to the staff what they understand and is offered opportunities to ask questions. The participant will then insert their signature or their thumbprint on the form in the presence of an adult witness, followed by the obtaining of the signature or thumbprint of the adult witness. Following informed consent to participate in the study, the staff will enroll eligible couples in the study, conduct baseline assessments and randomly assign them to the intervention or enhanced usual care arm, as shown in Fig 3.

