#### Exclusion criteria.

Exclusion criteria include: i) husband has severe alcohol dependence (Severity of Alcohol Dependence Questionnaire, [69] SADQ ≥ 31) or is at risk of severe withdrawal symptoms based on Clinical Institute Withdrawal Assessment for Alcohol Scale–Revised [70] (CIWA-AR); ii) significant medical problems that will make the couple unable to participate in the intervention sessions; iii) cognitive problems (Short-Blessed Cognitive Test [71] score ≤7); iv) past year history of IPV severe enough to result in hospitalization; or v) wife is positive for AUD (AUDIT-C ≥ 4) at screening [68].

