### Training

All nurses delivering the intervention will receive intensive training in MI and BCT from the study intervention coordinator who is a trained clinical psychologist (author MA), under the guidance of co-authors (MH and KS) with expertise in BCT and co-authors ([name] and [name] and ME) with expertise in MI. Staff will also be trained by a study consultant with expertise in gender-based health, as well as safety procedures for responding to participant distress. Training will takes place over one month and includes a combination of didactics, video, and interactive role-plays. Trained nurses-counselors will be tested on general counseling skills, MI-specific skills, and session-by-session MI + BCT manual components and participant handouts, followed by repeated mock sessions with supervisor and peer feedback. At least two independent raters will use intervention fidelity checklists to observe and evaluate each nurse’s delivery of all sessions and certify them to be nurse-counselors before they begin delivering the intervention to enrolled couples. Nurses who do not meet the threshold on the fidelity checklist will be re-trained until they meet certification criteria.

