#### Control arm.

Our prior work in India has shown a lack of availability of care for AUD and/or IPV in PHCs, as well as lack of adherence to existing protocols. [76,77] To meet ethical guidelines, the control arm participants receive a single session of enhanced usual care, consisting of (1) validation and safety planning for the wife; (2) referrals to provide medical-legal and shelter support; and (3) a brief educational intervention to the husband on alcohol use, based on the World Health Organization’s manual for managing AUD in primary care settings, [74] and a referral to tertiary care mental health (NIMHANS) and addictions treatment center. These will be carried out within two months of the baseline assessment by a trained nurse practitioner who is not involved in delivering the intervention.

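### The stated provision for people turned away at screening names no legal or shelter referral, even for women excluded because of violence that led to hospital or the police

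*Protocol article*

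**What the plan says.** Recruitment & retention sets one rule for everyone turned away with a positive screen: "All participants who are ineligible for the study but screen positive for AUD and/or IPV will receive a brief educational session [74]". Such people are also referred to NIMHANS. The section describes NIMHANS as an institute that "offers counseling and psychiatry services as well as a dedicated de-addiction treatment for severe alcohol dependence and alcohol withdrawal".

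That group includes women excluded for the severity of the violence. The exclusion list names "past year history of IPV severe enough to result in hospitalization". Recruitment & retention is wider: the wife's violence screen is used "to rule out violence severe enough to have resulted in the woman being admitted at a hospital or lodging police complaints". Participant safety explains that severe cases are left out because the intervention was not built for them.

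Wives randomized to control receive validation, safety planning and medical-legal and shelter referrals (Control arm), delivered by a trained nurse practitioner. The reason given is an ethical one and begins: "Our prior work in India has shown a lack of availability of care for AUD and/or IPV in PHCs". The same section cites reference 74 as the WHO manual for managing alcohol use disorder in primary care, as the basis for the husband's alcohol education.

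Participant safety adds two referral routes. One sends a wife who is already enrolled and wants more support to legal or integrated organizations. The other sends participants whose violence worsens to local integrated services.

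**The concern.** The study seeks these women out. Community health workers identify couples they know to be experiencing violence and bring them in, and screening then asks the wife about it. If she reports violence that led to hospital admission or a police complaint, she is excluded. What the article then names for her is education from an alcohol manual and a mental health and addiction referral.

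Followed as written, the rule names less violence-specific help for a woman excluded because of severe violence than the control arm gives to wives from whom those cases have been screened out. The ground given for the control package, the lack of care in primary health centers, applies equally to women screened out in the same catchment areas. The stake is participant safety. Estimand, power and analysis are untouched.

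**Working it through.** The protocol states no figure to reproduce here, so the check is a comparison of text followed by arithmetic for scale.

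**What each group is named to receive**

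- *Ineligible, positive for AUD and/or IPV* (Recruitment & retention): brief educational session citing reference 74, and NIMHANS referral. No safety planning or medical-legal or shelter referral is named.
- *Control-arm wife* (Control arm): validation, safety planning, and medical-legal and shelter referrals.
- *Enrolled wife asking for more support* (Participant safety): legal or integrated support organizations.
- *Participant whose violence worsens* (Participant safety): local integrated services.

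**Which rule governs a woman excluded for severe violence?**

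1. She is ineligible and IPV-positive, so the first rule applies to her by its own terms.
2. The session's only cited source is the alcohol manual, as Control arm shows.
3. The third route excludes her because she is not enrolled.
4. The fourth is triggered by worsening, not by severity at screening, and the article describes no follow-up of screened-out women that would detect worsening.

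No medical-legal or shelter referral is therefore named for her.

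**Scale**

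- Inputs: "we conservatively estimate needing to screen 2,350 couples to enroll 400"; recruitment from July 2023 to September 2026 (Trial status); eight to nine health centers (Study setting).
- Couples not enrolled: 2,350 − 400 = 1,950, or 1,950 / 2,350 = 83.0%.
- Recruitment months, both end months counted: 6 + 12 + 12 + 9 = 39.
- Rate: 1,950 / 39 = 50 couples a month; per center, 50 / 9 = 5.6 to 50 / 8 = 6.3 a month.

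This is an upper bound on the plan's own screening estimate and covers every reason for non-enrollment. The document does not say what share is IPV-positive or excluded for severe violence.

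**Staff time** (minutes per woman are assumptions)

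- Referral information, 2 to 5 minutes, for all 50 women: 100 to 250 minutes, or 1.7 to 4.2 hours a month across all sites.
- Safety planning, 10 to 30 minutes, for each 1% of non-enrolled couples that is a severe exclusion (0.5 women a month): 5 to 15 minutes a month.
- Extreme case, safety planning for all 50: 500 to 1,500 minutes, or 8.3 to 25 hours a month.

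**The case against.** The strongest reply is that this is a condensed article. Handling of screen failures who disclose violence belongs in a safety procedure. The article points to a Data and Safety Monitoring Plan with detailed risk provisions, and ethics boards reviewed the study materials. This stands as a limit: the unseen documents may already provide what is asked. It does not remove the point, because the article is not silent. It states a rule for this group, and the rule fits IPV-positive women poorly.

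Second, the control package is the comparator for randomized couples, and the document sets no equal standard for people never enrolled. That is correct. A reader might infer that the sections contradict each other; they do not, since they cover different groups.

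Third, some help exists. NIMHANS offers counseling, staff are trained in "safety procedures for responding to participant distress", and the article uses the word participants for ineligible people too, so the worsening-violence referral could be read to reach them. A reader might therefore conclude that these women get nothing, which the text does not support. What is missing from the stated rule is specifically legal, shelter and safety help.

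Fourth, more intervention can do harm. The Discussion warns that women-only programs may increase violence if the husband learns of them, and couples are brought in together. Control arm assigns its session to a trained nurse practitioner, while research staff do the screening. It is tempting to ask for safety planning for every such woman by staff assumed to be ready for it; the document does not establish that training. This objection stands and narrows the remedy.

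Finally, admission or a police complaint is only a proxy for severity. Enrolled women may suffer serious violence that reached neither, so they cannot simply be called lower-risk.

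**Conclusion.** The point holds in a limited form. For women excluded because violence led to hospitalization or a police complaint, the stated rule names only education based on an alcohol manual and a NIMHANS referral. Medical-legal and shelter referrals already exist in the trial, and the stated rule does not extend them to these women.

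Its size cannot be given. The figure of 1,950 non-enrolled couples (50 a month) is a ceiling for all reasons together; reading it as the number of women left without help would be wrong. The conclusion assumes that the article's sentence is the whole provision for this group, which the full protocol or monitoring plan might disprove. It is a worthwhile safety amendment with no statistical consequence.

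**What to change.** Amend Recruitment & retention in two parts.

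1. Offer ineligible IPV-positive women, above all those excluded for hospitalization or a police complaint, the medical-legal and shelter referrals already used in the trial, in addition to NIMHANS. The offer should be optional, verbal and private. The setting exists: "Research staff will screen and obtain informed consent with the spouses separately". Private delivery also keeps the communication-focused framing toward the husband.
2. Offer brief safety planning only to severe cases who want it, where a trained person is available and it can be done without alerting the husband.

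If the full protocol or monitoring plan already provides this, one sentence saying so is enough.

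The cost is a short wording change and a few minutes per woman, at most 1.7 to 4.2 staff hours a month for the referral offer under the assumed times. Safety planning adds time in proportion to the unknown number of severe cases and needs someone trained to do it. The main downside is the risk that the husband finds out, which is why the offer must be private and brief. Sample size, randomization and analysis stay as they are.

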### Training

All nurses delivering the intervention will receive intensive training in MI and BCT from the study intervention coordinator who is a trained clinical psychologist (author MA), under the guidance of co-authors (MH and KS) with expertise in BCT and co-authors ([name] and [name] and ME) with expertise in MI. Staff will also be trained by a study consultant with expertise in gender-based health, as well as safety procedures for responding to participant distress. Training will takes place over one month and includes a combination of didactics, video, and interactive role-plays. Trained nurses-counselors will be tested on general counseling skills, MI-specific skills, and session-by-session MI + BCT manual components and participant handouts, followed by repeated mock sessions with supervisor and peer feedback. At least two independent raters will use intervention fidelity checklists to observe and evaluate each nurse’s delivery of all sessions and certify them to be nurse-counselors before they begin delivering the intervention to enrolled couples. Nurses who do not meet the threshold on the fidelity checklist will be re-trained until they meet certification criteria.

### Procedures

#### Intervention arm.

The Harmony intervention consists of 10, hour-long sessions delivered once weekly (Table 1) during a three- to five-month period. Initially, the husband receives three individual sessions of MI as well as one session jointly with his wife to address alcohol use, which is the standard primary care-based intervention to reduce AUD in community populations. The MI sessions focus on specific individual, interpersonal, and social factors driving disordered alcohol use by utilizing the four-step process of engaging, focusing, evoking and planning. [62] The intervention is presented to participants as a means of improving the couple’s communication and marital relationship (rather than explicitly as an AUD/IPV intervention) to reduce the potential stigma of attending sessions focused on AUD/IPV. The husband receives training in drink refusal, emotion regulation, problem-solving, and urge management skills. The nurse-counselor co-constructs a weekly change-and-action plan to help the husband use these skills between sessions. The nurse-counselor invites the wife to the fourth MI session, which orients the couple to lapse and relapse prevention and management. This joint session marks the transition to BCT. Following this, both spouses receive six sessions of BCT together [40] to improve interpersonal communication, caring, and trust.

**Table 1 pone.0335332.t001:** Summary of MI* + *BCT Intervention.

Session Number	Session Content	Session Participants
1-4	• Engaging, focusing, evoking and planning • Drink refusal, emotion regulation, problem solving, and urge management skills • Relapse prevention and management	Husband in 1–3 Husband and Wife in 4
5	• Trust: Daily Trust Contract	Husband and Wife
6	• Coping: Catching yourself, time-out, diaphragmatic breathing, relaxation, positive self-talk	Husband and Wife
7	• Effective communication • Joint problem-solving	Husband and Wife
8	• Caring: Catching your partner being nice and telling them	Husband and Wife
9	• Active listening • Expressing feelings directly using I-statements	Husband and Wife
10	• Review and wrap-up	Husband and Wife

The first BCT session focuses on the development of a daily trust contract in which the husband verbally commits to reducing his drinking while his wife acknowledges her support and appreciation. The second BCT session discusses specific strategies to cope with stress and reduced alcohol use (including time-outs, a diaphragmatic breathing exercise, and engaging in positive self-talk). Effective communication and joint problem-solving are core components of session three, followed by mutually caring activities in BCT session 4. The fifth BCT session expands on effective communication by helping couples learn and practice active listening and using “I” statements to reciprocally express feelings in a direct manner. The last BCT session includes review and wrap-up, with couples revisiting useful topics and skills and planning for long-term improvement in alcohol use and relationship quality. All sessions include role plays and end with simple homework practice assignments. In addition, nurse-counselors use in-session charts with visuals and limited text, due to variability in participant literacy levels, to enhance participant comprehension and reinforce lessons and skills taught.

The intervention window is five months to allow for missed visits due to family holidays, illness, and travel. During their first visit, the couple is informed that session scheduling attempts will be discontinued after five months, regardless of the number of sessions attended at that point.

#### Intervention fidelity.

Motivational Interviewing Treatment Integrity (MITI) [75] will be used to ensure MI fidelity, rating all nurse-counselors on content coverage, MI-specific skills, and general counseling skills. For BCT, a standard checklist updated from the pilot [36] will be used to evaluate nurse-counselors on content coverage and overall session delivery quality. These checklists will be used to certify the nurse-counselors before they begin delivering the intervention in the trial and to assess ongoing sessions during the study. A clinical psychologist will directly observe and review 10% of all sessions per nurse-counselor, including 20 and 30 randomly selected MI and BCT sessions, respectively. Daily check-ins with each nurse-counselor will be carried out by the clinical psychologist to track couples and discuss challenges, if any, with regards to scheduling and conducting the sessions. Weekly group supervision sessions will include presentation of each intervention “case” or couple by the respective nurse-counselor and a discussion of session content, processes, and strategies for addressing challenges.

#### Control arm.

Our prior work in India has shown a lack of availability of care for AUD and/or IPV in PHCs, as well as lack of adherence to existing protocols. [76,77] To meet ethical guidelines, the control arm participants receive a single session of enhanced usual care, consisting of (1) validation and safety planning for the wife; (2) referrals to provide medical-legal and shelter support; and (3) a brief educational intervention to the husband on alcohol use, based on the World Health Organization’s manual for managing AUD in primary care settings, [74] and a referral to tertiary care mental health (NIMHANS) and addictions treatment center. These will be carried out within two months of the baseline assessment by a trained nurse practitioner who is not involved in delivering the intervention.

### Outcomes

#### Primary.

Primary outcome measures include: 1) mean scores on the Indian Family Violence and Control Scale (IFVCS) [41] and 2) mean scores on the Alcohol Use Disorders Identification Test (AUDIT) [77,78].

#### Secondary.

Key secondary outcome measures include number of days (0–7) with a negative breathalyzer test over a one-week period prior to each follow-up interview and scores on the Communications Patterns Questionnaire (CPQ) [79] to assess couples’ communication and related behaviors during and after conflict interactions. A complete list of measures is included in Fig 1 and Table 2. All scales have been validated for use in India.

**Table 2 pone.0335332.t002:** Outcome variables, measures and intervention strategies.

Key Model Variables	Husband or Wife	Description of Scales	Intervention Strategies
**Demographics** *BL*	H, W	Age, years married, arranged marriage, children, living situation, education, religion, and income	
**Self-Efficacy** *BL, 6mo, 12mo*	H	Situational Confidence Questionnaire (SCQ) [80]: eight items assessing self-efficacy in resisting urge to drink heavily in alcohol-related situations	• Elicit participant-specific motivations, fears, and ambivalence and evoke change talk to facilitate behavior change (MI) • Collaboratively develop plan for change and problem-solve barriers (MI) • Provide coping skills to resist drinking urges (BCT)
**Motivation to Change** *BL, 6mo,12mo*	H	12-item Readiness to Change questionnaire for use in brief, opportunistic interventions among excessive drinkers [81]	
**Coping Skills** *BL, 6mo, 12mo*	H, W	Brief COPE [82]: a 28-item scale that assesses the use of different coping strategies for challenging situations	
**Alcohol Consumption and Dependence** *Primary and secondary outcome: quarterly*	H	Alcohol Use Disorders Identification Test (AUDIT) [78,83]:10 items measuring alcohol consumption, drinking behaviors and alcohol-related problems Number of negative breathalyzer tests in 7 consecutive days prior to quantitative interview	• Facilitate increased awareness of drinking patterns (MI) • Elicit negative consequences of alcohol use (MI) • Support reduced alcohol use (MI) • Develop daily trust contract for accountability to maintain sobriety (BCT) • Review positive reasons for sobriety, distracting activities and positive self-talk (BCT) • Identify interpersonal triggers and ways to avoid alcohol use (BCT)
**Alcohol Expectancies** *BL, 6mo, 12mo*	H	Alcohol Outcome Expectancies questionnaire: 38 items assessing positive and negative alcohol use expectancies [84,85]	
**Context of Drinking** *BL, 6mo, 12mo*	H	Five items measuring social and interpersonal contexts of alcohol consumption [86,87]	
**Context of IPV** *BL, 6mo, 12mo*	H, W	14 items measuring social and interpersonal contexts of IPV [86–88]	• Promote positive relationship dynamics, provide safe discussion space to explore conflict, violence, and relationship impact (BCT)
**Attitudes Towards Violence** *BL*	H	Gender-Equitable Men (GEM) scale, IPV subscale: 4 items assessing attitudes towards gender norms in intimate relationships [10,89]	
**Intimate Partner Violence** *Primary Outcome: BL, 6mo, 12mo*	W	Indian Family Violence and Control Scale (IFVCS): 63 items to measuring control, psychological, physical, and sexual violence/coercion [40]	• Link violence to stressors and drinking patterns (BCT)
**Marital Relationship** *BL, 6mo, 12mo*	H, W	17 items assessing the frequency of positive interactions between spouses in the past month [36,90,91]	• Build skills to improve relationship dynamics (BCT)
**Communication Skills** *Secondary outcome:* *quarterly*	H, W	Communications Patterns Questionnaire (CPQ): 35 items assessing couple’s behavior patterns during and after conflict interactions [79]	• Teach active listening skills (BCT) • Promote healthy communication (BCT)
**Anger Management** *BL, 6mo, 12mo*	H	Clinical Anger Scale (CAS): 21 items assessing clinical anger and treatment progress [92]	• Promote emotion regulation through improved communication (BCT)
**Family and Financial Stress** *BL, 6mo, 12mo*	H, W	Chronic Strain Checklist (CSC): 23 items assessing family, marital, financial and work-related stressors [93,94]	• Identify life stressors and their relation to relationship problems and drinking patterns (MI, BCT)
**Decision Making Power** *BL, 6mo, 12mo*	H, W	Sexual Relationship Power Scale (SRPS): 9 items assessing decision-making power in the relationship [95] and three additional items on financial decisions	• Facilitate joint financial and general decision-making (BCT)
**Stigma** *BL, 6mo, 12mo*	H, W	• Alcohol-adapted Perceived Devaluation-Discrimination scale (PDD), adapted: 13 items assessing perceived alcohol stigma [96] • IPV Stigma Scale: 20 items assessing or internalized, anticipated, and perpetrator stigma, and isolation [97]	• Increase knowledge and identification of consequences of stigma related to alcohol use and interpersonal violence (BCT)
**Anxiety** *BL, 6mo, 12mo* **Depression** *quarterly*	H, W	• Generalized Anxiety Disorder Scale (GAD-7): 7 items assessing DSM-specific anxiety symptoms [98] • Personal Health Questionnaire (PHQ-9): 9 items assessing DSM-specific depressive symptoms [99]	• Improve coping to reduce stress and reduce drinking (MI, BCT)
**Gender Norms** *BL*	H	Gender-Equitable Men (GEM): 23 items assessing attitudes toward gender-equitable and inequitable norms [89,100]	Theoretical Moderators
**Impulsivity** *BL*	H	Barratt Impulsiveness Scale, short form (BIS-15): 15 items assessing personality and behavioral constructs of impulsivity [101]	
**Contraception** *BL*	H, W	8 items assessing contraceptive use with spouse (for women) and with spouse and other sexual partners (for men).	

H = Husband; W = Wife; BL = Baseline; 6mo = 6 months; 12mo = 12 months.

